### Trial design {8}

This trial is designed as an open-label parallel two-group cluster randomized trial with a 1:1 allocation ratio.

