#### Sample size {14}

A total of 110 facilities participate in the trial. Out of these 110, 50% will be randomly selected for the treatment. Within each facility, up to 8 under-5 sick child visits will be observed. We anticipate an average of 6 direct observations in each facility, resulting in a sample of 660 direct observations for our primary outcome. At baseline, compliance with diagnostic protocols was 10%. The study is powered to detect a 15% point increase in diagnostic compliance (from 10 to 25%) with *p* = 0.9, assuming alpha = 0.05 and an intra-class correlation of 0.2 (DEFF of 2).

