### Assignment of interventions: allocation

#### Sequence generation {16a}

Randomization was done at the health facility (cluster) level. Within each health zone, 50% of health centers were randomly selected for the intervention using a simple random number draw created in the Stata statistical software package by GS.

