## Statistical methods

### Statistical methods for primary and secondary outcomes {20a}

Multi-level regression models will be used to analyze the primary and secondary study outcomes. The primary outcome (compliance) will be a binary indicator for (observed) the health care worker completing at least 8 out of 10 diagnostic processes foreseen in the IMCI guidelines during an observed consultation. This indicator will be regressed against the randomized facility-level treatment. The empirical model will look as follows:
$$ {Y}_{if}=\alpha +\beta {V}_f+{\varepsilon}_{if} $$

where *Y*_*if*_ is the quality score (1 if compliant, 0 otherwise) of consultation *i* observed in facility *f*, and *V*_*f*_ is an indicator for facilities having received the vignettes intervention (*V* = 1 if yes and 0 otherwise). *β* is the main parameter of interest and captures the changes in the average quality or compliance in response to the intervention.

The secondary outcomes will be continuous knowledge and compliance scores, which will be based on a detailed assessment of medical staff. The unit of analysis for the knowledge outcome is a health care worker rather than a single consultation, with up to 5 health care workers assessed in each facility.

To account for the treatment assignment at the facility level, standard errors will be clustered at the facility level using Huber’s cluster-robust standard errors in all analyses.

Given that facilities were randomly assigned to treatment and control groups, the risk of residual confounding is low—we will however also estimate a series of adjusted models to ensure the robustness of our results as explained in the next paragraph.

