### Methods for additional analyses (e.g., subgroup analyses) {20b}

To improve the precision of our estimates, we will also estimate the adjusted models where we control for health care worker characteristics (age, training, position, and time at the facility) as well as facility characteristics including facility quality scores at baseline.

In addition, we will conduct a subgroup analysis comparing only medical staff members that were directly assessed in treatment facilities to medical staff in the control group. We will also conduct a stratified analysis at the hospital and health center levels.

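### Huber cluster-robust errors are fixed for every analysis, including a hospital-only one. If hospitals are few or unevenly split, those errors can be too small

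*Protocol article*

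**What the plan says.** Under Statistical methods for primary and secondary outcomes {20a}, the protocol article regresses a binary compliance indicator on the facility-level treatment and prescribes Huber's "cluster-robust standard errors in all analyses", clustered by facility. It states no finite-sample factor, reference distribution or degrees of freedom.

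Methods for additional analyses {20b} adds: "We will also conduct a stratified analysis at the hospital and health center levels". Read together, the two sections apply the Huber rule to a hospital-only estimate.

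Sample size {14} gives the total: "A total of 110 facilities participate in the trial". Nowhere does the article say how many of these are hospitals. Trial design {8} describes an "open-label parallel two-group cluster randomized trial with a 1:1 allocation ratio". Sequence generation {16a} describes the draw as follows: "Within each health zone, 50% of health centers were randomly selected for the intervention". It does not mention hospitals and does not name facility type as a randomization stratum.

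**The concern.** The Huber sandwich is justified when clusters are many. It builds the variance from squared residuals, which are too small on average because each arm's mean is fitted to the same few facilities. With 110 facilities this shrinkage is negligible, but with a handful it is not, and a lopsided split makes it worse because the smaller arm dominates the true variance.

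A low compliance rate adds a second difficulty. If no hospital in an arm has a compliant visit, that arm's residuals are all zero and it adds nothing to the standard error.

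At stake is the interval and p-value of the hospital estimate. A chance difference between a few hospitals could be reported as evidence that the incentive works, or fails, in hospitals. Whether the stratum analysis is worthwhile, or needs an interaction test, is a separate matter.

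**Working it through.** **Inputs from the protocol article.** Sample size {14} gives 110 facilities, a mean of 6 and a maximum of 8 visits per facility, ICC 0.2, baseline compliance of 10%, a target of 25% and alpha 0.05.

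**Assumptions.** The test is two-sided. The number of hospitals G and the arm split are unknown, so a range is shown. Each hospital supplies 8 visits. Null compliance is 10% or 25%; the 25% is the plan's treated-arm target, used here only as a second plausible rate.

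**The plan's own figure.** DEFF = 1 + (6 − 1) × 0.2 = 2.0, as stated. The plan gives no figure for the hospital stratum.

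**Size of the shrinkage.** Take g1 and g2 facilities with equal numbers of visits and facility-mean variance σ². The true variance of the difference is σ²(1/g1 + 1/g2). The expected Huber variance is σ²[(g1 − 1)/g1² + (g2 − 1)/g2²].

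- 4 v 4: 0.375/0.500 = 0.750, so the standard error is √0.750 = 0.87 of its true size.
- 2 v 6: 0.389/0.667 = 0.583, giving √0.583 = 0.76.
- 55 v 55: the ratio is 54/55 = 0.982, giving √0.982 = 0.99.

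The common finite-sample factor is G/(G − 1) × (N − 1)/(N − 2). For 8 hospitals with 64 visits it is 8/7 × 63/62 = 1.161. The variance ratio becomes 0.750 × 1.161 = 0.87 at 4 v 4, but only 0.583 × 1.161 = 0.68 at 2 v 6. The factor depends on G and N alone, so it cannot see the imbalance.

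**Type I error with normal facility means, even split, z = 1.96.** The Huber statistic equals a t(G − 2) variable times √(g/(g − 1)). The error is therefore P(|t(G − 2)| > 1.96 × √((g − 1)/g)).

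- 4 v 4: P(|t(6)| > 1.697) = 14.1%.
- 6 v 6: P(|t(10)| > 1.789) = 10.4%.
- 10 v 10: P(|t(18)| > 1.859) = 7.9%.
- 55 v 55: P(|t(108)| > 1.942) = 5.5%.

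**Type I error for the binary outcome.** I used a beta-binomial simulation with no effect, ICC 0.2, 8 visits per hospital (6 in the last row) and 40,000 trials per setting. Entries are percentages at 10% / 25% compliance.

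| Hospitals by arm | Huber, z | Huber with factor, t(G−1) | CR2, Satterthwaite df | t-test on facility means, G−2 df |
|---|---|---|---|---|
| 3 v 3 | 15.3 / 18.0 | 3.4 / 7.9 | 2.3 / 4.8 | 2.3 / 4.8 |
| 4 v 4 | 11.8 / 13.9 | 4.5 / 6.8 | 3.2 / 4.8 | 3.2 / 4.8 |
| 6 v 6 | 8.7 / 10.0 | 4.1 / 5.8 | 3.4 / 4.8 | 3.4 / 4.8 |
| 10 v 10 | 7.4 / 7.7 | 5.0 / 5.5 | 4.2 / 4.9 | 4.2 / 4.9 |
| 15 v 15 | 6.6 / 6.9 | 5.0 / 5.3 | 4.6 / 5.0 | 4.6 / 5.0 |
| 2 v 6 | 19.7 / 24.3 | 8.5 / 14.8 | 1.2 / 1.4 | 4.3 / 4.9 |
| 3 v 9 | 17.0 / 17.3 | 10.0 / 12.0 | 2.1 / 4.1 | 4.2 / 4.4 |
| 4 v 8 | 12.4 / 12.8 | 6.4 / 8.0 | 3.1 / 4.9 | 3.9 / 4.8 |
| 7 v 13 | 9.2 / 9.2 | 6.4 / 6.7 | 4.8 / 5.2 | 4.2 / 4.9 |
| 55 v 55 | 5.3 / 5.6 | 4.9 / 5.2 | 4.9 / 5.1 | 4.9 / 5.1 |

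At 4 v 4 and 10% compliance, at least one arm has no compliant visit in about 26% of simulated trials. With even splits and equal numbers of visits, CR2 and the facility-mean t-test coincide.

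**The case against.** **The number of hospitals is unknown.** A reader might infer that the hospital stratum has few clusters and that its intervals will be too short. The article supports neither as fact. With 40 evenly split facilities (4 to 8 visits each), even the uncorrected sandwich with z gives only 6.2 to 6.7%. This objection stands, and the point is conditional on it.

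**The worst figures need a procedure that the article does not specify.** It names the Huber estimator but neither excludes a finite-sample factor nor prescribes a normal reference. With the factor and t(G − 1), even splits and 10% compliance, the error is 3.4 to 5.0% for 6 to 20 hospitals, which is no material inflation. This stands too. It does not cover uneven splits, where the factor leaves 6.4 to 14.8%, or 3 v 3 and 4 v 4 at 25% compliance (7.9 and 6.8%).

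**The uneven split is not established.** A reader might infer that chance alone decided how many hospitals fell in each arm. Sequence generation {16a} speaks only of health centers, so the allocation of hospitals is not described. An uneven split is possible but not shown.

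**This is detail for an analysis plan.** A small-sample correction often is, and CR2 is itself a cluster-robust estimator, so naming it refines the rule. But the article has already named one estimator and extended it to every analysis. Narrowing that scope is a change to what is written.

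**The remedies are imperfect.** CR2 rescales residuals, and zero residuals stay zero, so an arm without compliant visits still adds nothing. Both remedies are conservative at 10% compliance with very few hospitals (2.3% at 3 v 3), and CR2 with Satterthwaite degrees of freedom is very conservative at 2 v 6 (1.2 to 1.4%). This is a real cost.

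**Conclusion.** The point holds in conditional form. The stated rule covers a hospital-only analysis whose number of clusters and arm split are not given. If hospitals are below about 20 or unevenly split, the Huber errors can be too small.

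- **Uncorrected sandwich, normal reference:** about 9 to 18% type I error for 6 to 12 evenly split hospitals.
- **Finite-sample factor with t(G − 1):** about 3.5 to 8% for even splits and about 6.5 to 15% for the uneven splits examined.

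These figures rest on the assumed number of hospitals, ICC 0.2, 8 visits each (the plan's maximum) and a null compliance of 10 to 25%.

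A reader might also take this as a flaw in the primary analysis. It is not: with 110 facilities the rule gives about 5.3 to 5.6%. The weight is that of a cheap improvement to one secondary analysis.

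**What to change.** Keep the Huber rule for the full sample. Add one sentence to the statistical methods. For the hospital stratum, and any other analysis with few facilities (about 20 or fewer, or a clearly uneven split), use either bias-reduced (CR2) cluster-robust errors with Satterthwaite degrees of freedom or a t-test on facility means with G − 2 degrees of freedom. Choose one before the endline data are examined. Under a very lopsided split the facility-mean t-test is the less conservative of the two, but it assumes similar between-facility variance in both arms.

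Report the number of hospitals per arm, and any arm with no compliant visit, beside the estimate.

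No new data are needed and the primary analysis does not change. The cost is a wider interval in the hospital stratum, and a somewhat conservative test if hospitals are very few and compliance stays near 10%.

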#### Outcomes {12}

The primary study outcome is compliance with under-5 diagnostic guidelines. Compliance will be measured through up to 8 direct observations of under-5 sick child visits at each facility collected over a 4-day period. For each visit, 10 diagnostic process steps will be measured. Compliance will be defined as at least 8 out of 10 diagnostic processes completed.

Secondary outcomes will be health care worker’s knowledge of IMCI protocols and compliance with the IMCI treatment guidelines. IMCI knowledge will be assessed through a series of vignettes provided to the medical staff. For compliance with treatment guidelines, we will focus on the administration of antibiotics and anti-malarials and referrals to higher level health centers as well as compliance with all diagnostics steps specified in the IMCI guidelines.

Primary and secondary outcomes will be measured as part of a facility survey that will be conducted between May and December 2021. All facilities in the treatment and control areas will be visited by an assessor team for 3–5 days, who directly observe all under-5 sick child visits up to the targeted 8 observations during this facility visit. For smaller facilities, we expect only about one visit per day—for larger facilities, the target of 8 visits can likely be completed within less than two days.

Similar assessments have been conducted through a baseline survey in 2018. These prior assessments will be used to assess baseline balance; the average 2018 quality scores will also be used as controls in adjusted impact estimates.

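### The primary model omits the 2018 facility score and the randomisation zones: a valid analysis that gives up some precision it could have at little cost

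*Protocol article*

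**What the plan says.** The section Statistical methods for primary and secondary outcomes {20a} writes out one equation for the primary outcome: an intercept, the treatment indicator and an error term, with standard errors clustered by facility. The treatment coefficient is named as the quantity of main interest. Because facilities were randomised, confounding is considered unlikely, and the section adds: "we will however also estimate a series of adjusted models to ensure the robustness of our results".

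The 2018 survey is used elsewhere. Outcomes {12} says it will serve to check balance and that "the average 2018 quality scores will also be used as controls in adjusted impact estimates". Methods for additional analyses {20b} lists the covariates of the adjusted models. They are worker age, training, position and time at the facility, together with "facility characteristics including facility quality scores at baseline". That section gives precision as the purpose.

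Sequence generation {16a} says that half of the health centres within each health zone were drawn for the intervention. No model in the article mentions health zone.

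**The concern.** A facility measure taken before the intervention, if it resembles the outcome, is usually the most useful covariate a cluster trial has. The strata used to randomise are the next candidate. Here {20b} acknowledges that adjustment buys precision, yet the result that will be quoted as the trial's answer does not benefit from it. The only model described as containing the baseline also contains worker characteristics. Their timing is not stated and, if they are recorded at endline, the intervention could have affected them. So the article offers a headline estimate without the baseline and an adjusted estimate with questionable covariates, but not the simple model in between.

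What is at stake is the width of the confidence interval, chiefly if the true effect is smaller than the 15 points planned for.

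**Working it through.** **Inputs from Sample size {14}.** "A total of 110 facilities participate in the trial". "Out of these 110, 50% will be randomly selected for the treatment", so 55 per arm. "We anticipate an average of 6 direct observations in each facility, resulting in a sample of 660 direct observations for our primary outcome", so 330 per arm. Control compliance is 10% and the target 25%. Alpha is 0.05 (taken as two-sided; the article does not say), the intra-class correlation 0.2, the design effect 2 and the stated power 0.9.

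**Step 1: the plan's own figure, without covariates.**
- Design effect = 1 + (6 − 1) × 0.2 = 2.0, as stated.
- Effective size per arm = 330 / 2 = 165.
- Standard error under the null (pooled 17.5%) = √(2 × 0.175 × 0.825 / 165) = 0.0418. Under the alternative it is √((0.10 × 0.90 + 0.25 × 0.75) / 165) = 0.0410.
- Power = Φ((0.15 − 1.96 × 0.0418) / 0.0410) = Φ(1.66) ≈ 95.1%.

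This is not the stated 90%, but it errs on the safe side. Variants give 95.5% (unpooled), 95.2% (t with 108 degrees of freedom) and about 93.5% (continuity-corrected). For 90% power, 133 effective observations per arm are needed: 133 × 2 × 2 = 532 in total, against 660 planned. The difference detectable with 90% power is about 13.2 points.

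**Step 2: what a baseline covariate adds.** In a facility-level analysis of covariance the variance of the effect is multiplied by 1 − r², where r is the correlation between a facility's 2018 and endline means. The documents do not give r, so the values below are assumptions.

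| Assumed r | Variance factor 1 − r² | SE factor | Power, 10% v 25% | Power, 10% v 20% | Detectable at 90% power (points) |
|---|---|---|---|---|---|
| 0 | 1.00 | 1.000 | 95.1% | 72% | 13.2 |
| 0.1 | 0.99 | 0.995 | 95.3% | 73% | 13.1 |
| 0.3 | 0.91 | 0.954 | 96.7% | 76% | 12.5 |
| 0.5 | 0.75 | 0.866 | 98.7% | 84% | 11.2 |

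**Step 3: which r is plausible.** A mean of six visits with intra-class correlation 0.2 has reliability 0.2 / (0.2 + 0.8 / 6) = 0.60. If the 2018 means also rest on about six visits (not documented), r = 0.60 × the correlation of true facility levels over time.
- True correlation 0.2: r = 0.12, variance falls by 0.12² ≈ 1.4%.
- True correlation 0.5: r = 0.30, variance falls by 9%.
- True correlation 0.9: r = 0.54, variance falls by 29%.

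Under these assumptions r cannot exceed about 0.6.

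**Health zones.** Their contribution cannot be sized. The article gives neither the number of zones nor the variation between them.

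**The case against.** The strongest reply is that nothing is broken. An unadjusted comparison in a randomised trial is valid, the declared 15-point target exceeds its stated power without any covariate, and the article already plans baseline adjustment with precision in mind. All of that stands.

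Three stronger readings are tempting, and the documents do not support them:
- **The baseline is ignored.** It is not. {12} and {20b} pre-specify it for balance checks and as a covariate; only the headline equation lacks it.
- **Several models compete to be the main result.** {20a} names one coefficient as the main one, and the adjusted models sit under additional analyses. Calling them a robustness check in one section and a precision gain in another is loose, but the two aims are compatible.
- **The gain is large.** It may be only a few per cent. About three years separate the 2018 survey from the endline dates in {12}, the section on retention {18b} allows for staff leaving, and compliance is rare at baseline. The number of visits observed per facility in 2018 is not given. The intra-class correlation of 0.2 belongs to the binary outcome and need not apply to a differently scaled covariate.

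Two further cautions stand. It is not certain which 2018 variable exists for each facility. {12} speaks of similar assessments and {14} reports a 10% baseline for diagnostic compliance, but the abstract describes the survey as one of worker knowledge. The article also applies the term quality score to a programme checklist score, to a composite and to the binary outcome. And the survey clearly preceded the intervention, but the article places both survey and randomisation in 2018 without clearly giving their order.

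Timing also matters: {12} schedules endline for May to December 2021, and the protocol version is dated 22 February 2022. A change to the primary model would therefore be late.

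**Conclusion.** The point holds as a matter of efficiency. The primary model leaves out the 2018 facility measure and the zones used in randomisation, although the trial has both at hand in some form. There is no bias and no shortfall in power for the planned effect.

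The size is uncertain: a variance reduction of about 1% to 25% for assumed correlations of 0.1 to 0.5, or 0.1 to 2 points off the detectable difference of 13.2. The benefit is most visible for effects below the target. Power for a 10-point increase goes from 72% to between 73% and 84% over the same range. These figures assume a two-sided test, six visits per facility and the stated intra-class correlation, and they count nothing for the zones.

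**What to change.** Before anyone sees outcome data by arm, restate the primary model in {20a} as follows:

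- Treatment indicator, health-zone indicators and the facility's 2018 mean on the observed diagnostic-compliance measure, with facility-clustered standard errors. If that measure is not available for each facility, use one 2018 quality score, named and defined in the text.
- No health worker characteristics in the primary model, since they may be recorded after randomisation.
- Missing 2018 values handled by the chained-equations imputation already planned in {20c}, or by a simple facility-level method, with the choice stated.
- The unadjusted estimate reported as the sensitivity analysis, and one consistent purpose stated for the remaining adjusted models.

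The model stays linear, so the coefficient is still a difference in compliance proportions. No new data are needed if the 2018 facility measure is on file. The cost is a late change of primary model: it must be dated, documented and accompanied by a statement that outcomes by arm had not been seen. If that statement can no longer be made, keep the unadjusted model as primary and label this one as supporting. The zone indicators also use degrees of freedom, so the number of zones should be stated.

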### Interim analyses {21b}

No interim analysis is planned.

### Methods for additional analyses (e.g., subgroup analyses) {20b}

To improve the precision of our estimates, we will also estimate the adjusted models where we control for health care worker characteristics (age, training, position, and time at the facility) as well as facility characteristics including facility quality scores at baseline.

In addition, we will conduct a subgroup analysis comparing only medical staff members that were directly assessed in treatment facilities to medical staff in the control group. We will also conduct a stratified analysis at the hospital and health center levels.

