**Fig. 1 Fig1:**
[figure not shown]
Incentive structure

The knowledge assessments started in the last quarter of 2018 after the completion of the baseline survey. Figure 2 summarizes the overall timeline of the study as well as key measurement points.

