#### Plans to promote participant retention and complete follow-up {18b}

We do not foresee any closure of facilities. It is possible that some of the health care workers who were assessed as part of the knowledge tests no longer work at their prior facilities. This will not affect the sample size overall but will be considered when analyzing the data (larger treatment effects expected for medical staff directly selected for the knowledge test).

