## Discussion

This is to our knowledge the first trial investigating the effectiveness of financially incentivized knowledge vignettes on medical staff behavior. The 12 vignettes used in this study were developed by the study team specifically for this project and were designed to cover the most common infectious diseases, but of course do not cover the full mix of cases faced by the health care workers. It is also not clear if facilities directly reward or punish medical staff performance on these tests—no guidance was given to facilities with regard to this—detailed data on this as well as other aspects will be collected during endline.

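### The adjusted models offered for precision and robustness control for worker training, position and time at the facility, which are not tied to baseline and which the intervention could change

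*Protocol article*

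**What the plan says.** The primary model under Statistical methods for primary and secondary outcomes {20a} regresses consultation-level compliance on the facility's allocation alone. The same section then adds that "we will however also estimate a series of adjusted models to ensure the robustness of our results".

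The covariates are named under Methods for additional analyses {20b}, which gives a second purpose: "To improve the precision of our estimates, we will also estimate the adjusted models". The worker-level list reads "we control for health care worker characteristics (age, training, position, and time at the facility"), and the sentence continues "as well as facility characteristics including facility quality scores at baseline". The words on baseline attach to the quality scores. Outcomes {12} does the same: "the average 2018 quality scores will also be used as controls in adjusted impact estimates". No time point is given for any worker trait.

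Three other statements bear on timing and on what the intervention might change:

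- Intervention description {11a}: "The knowledge assessments started in the last quarter of 2018 after the completion of the baseline survey".
- Plans to promote participant retention {18b} allows that "some of the health care workers who were assessed as part of the knowledge tests no longer work at their prior facilities".
- Discussion: "It is also not clear if facilities directly reward or punish medical staff performance on these tests", and facilities were given no guidance on this.

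**The concern.** Covariate adjustment in a randomised trial sharpens an estimate without changing what it estimates, provided the covariates could not have been affected by allocation. Here the intervention pays the facility. Half of its quality score depends on how a randomly drawn worker performs on the knowledge test, and the bonus can reach 25% of the quantity-based payments (Intervention description {11a}). A facility in that position has a reason to care who sees children, in what role, and who stays.

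If it acts on that reason, part of the intervention's effect runs through staffing. Holding endline position or time in post constant removes that part. If those traits also share unmeasured causes with compliance, such as motivation, conditioning on them adds selection bias. The adjusted estimate would then answer a different question from the primary one. A gap between the two, or the absence of one, could not be read simply as a verdict on robustness, which is the use that {20a} gives these models.

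**Working it through.** **Step 1. When are the worker traits measured?** The article does not say, so this has to be inferred.

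- The model's unit is a consultation observed at endline ({20a}).
- Assessments began in October to December 2018. Outcomes {12} places the endline in May to December 2021, which is 29 to 38 months later. Participant timeline {17} gives the third and fourth quarters of 2020, which is 19 to 26 months later. On either date the covariates, if taken at endline, follow the start of the intervention by well over a year.
- A worker hired after 2018 has no 2018 value, and {18b} expects turnover.
- The direct observation tool in the Appendix records the type of worker at the observed visit (item 1.06). It also records a worker number referring to a separate questionnaire (item 1.04).

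Endline measurement is therefore a strong inference, not a stated fact.

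**Step 2. Which traits could allocation change?** Position and time at the facility can change for an individual and through who is in post. Training can change if it means courses attended, but hardly if it means professional qualification; the article does not define it. Age can shift only through who is in post.

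**Step 3. How large could the distortion be?** The plan gives no figure for this, so there is none to reproduce. The only plan figure used is the target in Sample size {14}: 10% to 25%, a total effect of 15 points.

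For one binary trait in a linear model,

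adjusted effect = total effect − s × g,

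where s is the difference between arms in the share of consultations held by workers with the trait, and g is the trait's coefficient for compliance given arm. Neither is in the document. Assumed ranges are s = 0 to 0.20 and g = 0.1 to 0.3. Adjusted effect in percentage points when the total effect is 15:

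| s | g = 0.1 | g = 0.2 | g = 0.3 |
|---|---|---|---|
| 0 | 15.0 | 15.0 | 15.0 |
| 0.05 | 14.5 | 14.0 | 13.5 |
| 0.10 | 14.0 | 13.0 | 12.0 |
| 0.20 | 13.0 | 11.0 | 9.0 |

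The largest loss is 0.20 × 0.3 = 0.06, or 6 of 15 points (40%). The smallest is zero. If s and g have opposite signs, the adjusted estimate exceeds the total effect, so the direction is not known either.

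**Step 4. What if the trait has no effect of its own?** Assume an unmeasured worker factor with prevalence one half. It raises compliance by c = 0.2 and the probability of the trait by b. Treatment raises the probability of the trait by a, around an average of 0.5. Then g = c × b × 0.25 / v, where v = 0.25 − a²/4 is the within-arm variance of the trait, and s = a.

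- a = 0.1, b = 0.2: g = 0.01/0.2475 = 0.040; adjusted effect 15 − 0.4 = 14.6 points.
- a = 0.1, b = 0.4: g = 0.02/0.2475 = 0.081; 15 − 0.8 = 14.2.
- a = 0.2, b = 0.2: g = 0.01/0.24 = 0.042; 15 − 0.8 = 14.2.
- a = 0.2, b = 0.4: g = 0.02/0.24 = 0.083; 15 − 1.7 = 13.3.

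A simulation with 2,000,000 draws per case gave 14.5, 14.2, 14.1 and 13.3, against unadjusted estimates of 14.9 to 15.0.

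**Step 5. What if the covariates are fixed before allocation?** Randomisation makes s zero in expectation, and both forms of bias disappear.

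**The case against.** The strongest reply is that little depends on these models. The effect of interest is the coefficient in the unadjusted model, and the adjusted models are additional. The article does not say that worker traits are taken at endline, and a condensed article may leave such timing to an analysis plan. Training may simply mean qualification. Turnover is mentioned without any suggestion that it differs by arm. The Discussion leaves reward and punishment open but mentions no hiring, reassignment or dismissal, and nothing shows that facilities control their own staffing.

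Most of this stands, and it rules out several stronger readings that a reader might infer:

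- **That the main result is biased.** It is not; the primary model contains no worker covariates.
- **That the document states endline measurement, or shows a staffing response.** It does neither. The first is an inference and the second only a possibility that the document leaves open.
- **That all four covariates are equally exposed.** Age is not, and training is uncertain.
- **That comparing adjusted with unadjusted estimates is uninformative.** That goes too far. If staff composition turns out similar in the two arms, agreement still carries some weight.

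What the reply does not remove is that the article itself names these covariates, gives the models a robustness purpose, and ties only the facility score to baseline. With consultation-level data and workers who may have joined after 2018, it is hard to see how the listed traits could all be baseline values.

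**Conclusion.** The point holds as a limited one that should be corrected. The adjusted models, as described, condition on worker traits that are in practice very probably measured after randomisation. A facility-level bonus could change at least position and time at the facility. If it does, the adjusted estimate departs from the total effect that the primary model targets and is not a clean test of robustness.

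The document does not allow the size to be computed. The range of 0 to 6 of 15 points rests wholly on the assumed values of s and g, on a single binary trait and on a linear model. It shows what could happen and is not an estimate for this trial. If staffing does not respond to the intervention, the bias is zero.

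**What to change.** In {20b}, and where {20a} refers to it, limit the adjusted models used for precision and robustness to variables fixed before allocation:

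- health zone, within which facilities were randomised ({16a});
- facility type (hospital or health centre), already used for the stratified analysis in {20b};
- the 2018 facility quality score, already planned as a control;
- 2018 facility-level staff characteristics, only if they were collected, which the article does not show.

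Report endline worker age, training, position and time at the facility by arm, so that readers can see whether staffing moved. Keep any model that adjusts for them as a separate exploratory analysis, labelled as conditioning on traits that may follow from treatment.

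The change is to wording only and needs no new data. The cost is a possible loss of precision from dropping worker-level covariates. The document gives no basis for saying how much of that the remaining covariates would recover.
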